#### Sample size determination

Prospective data of SBRT for unresectable head and neck cancer has demonstrated 1 year local control rates of 60% in the re-irradiation setting [20]. In the de novo setting, prospective data are limited and primarily consist of SBRT for early-stage glottis cancer, though in small, retrospective series predominantly for palliative purposes and/or for patients who are not candidates for standard of care definitive therapy, the reported 1 year local control rates range from 69–87% [21]. However, in the palliative setting or patients unfit for definitive therapy, a variety of other radiation regimens are often used, such as the “Quad-Shot” regimen, which generally have lower and/or less durable local control rates [23–25]. From these data, we estimate the historic control group 1 year local control rate to be 65%.

For the study group, unpublished analysis of a recently closed phase II trial at UCLA of dose-escalated SBRT to 55 Gray for treatment of previously radiated, recurrent head and neck cancer demonstrated a 1 year local control rate of 85% (NCT 03892720). We therefore hypothesize that patients enrolled in this trial will have a similar 1 year local control rate. A sample size of 38 patients will achieve 80% power to detect a 20% difference in the 1 year local control rate between PULSAR (85%) and historic control (65%), using a two-sided one-sample exact binomial test, at 0.05 significance level. Considering that some patients may become ineligible/drop out after enrollment, the target sample size is determined to be at least 43 patients. The 15 patients in the safety lead-in portion will be included in the sample should the study proceed past this portion.

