#### Populations for analyses

##### Full Analysis Set (FAS)

All efficacy analyses will be performed on the Full Analysis Set (FAS) following the Intent-To-Treat (ITT) principle. Patients who were enrolled but did not receive study treatment are included in the FAS population.

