#### Study endpoints

##### Primary endpoint

The primary endpoint is local control rate of the treated tumor target at 1 year, as measured from the date of enrollment. Local control will be evaluated by radiographic and/or clinical assessment as applicable. Participants who experience death or are lost to follow-up prior to 1 year will be assessed by their last radiographic/clinical evaluation.

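### The 80% power is computed for 38 patients after drop-outs, but the primary analysis set keeps all 43 enrolled, and the last-evaluation rule does not exclude a baseline evaluation

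*Protocol article*

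**What the plan says.** Three parts of the protocol article bear on this.

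- *Sample size determination*: "A sample size of 38 patients will achieve 80% power to detect a 20% difference in the 1 year local control rate", with a null of 65% and an alternative of 85%, "using a two-sided one-sample exact binomial test, at 0.05 significance level". Enrolment is then raised: "Considering that some patients may become ineligible/drop out after enrollment, the target sample size is determined to be at least 43 patients". No drop-out rate is given.
- *Populations for analyses*: "All efficacy analyses will be performed on the Full Analysis Set (FAS) following the Intent-To-Treat (ITT) principle". On untreated patients: "Patients who were enrolled but did not receive study treatment are included in the FAS population". The Evaluable Analysis Set (EAS), made up of treated, compliant patients without major deviations, has a supportive role. *Efficacy analyses* reports the primary endpoint on both sets, with an exact 95% interval.
- *Primary endpoint*: "Participants who experience death or are lost to follow-up prior to 1 year will be assessed by their last radiographic/clinical evaluation". Nothing requires that evaluation to come after baseline.

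**The concern.** Adding five patients to 38 to cover ineligibility and drop-out is the arithmetic of an analysis that leaves those patients out. The FAS leaves nobody out. Each of the five must then be scored as controlled or not controlled, and the power calculation covers neither case.

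The scoring rule adds a second difficulty. For a patient who is enrolled, never irradiated and then lost, the last evaluation may be the one at entry. No local failure has been seen by then, so the rule, followed literally, allows that patient to count as locally controlled at one year.

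At stake is the trial's one formal comparison, local control against 65%. Its operating characteristics depend on a scoring choice that is not fixed. If that choice is made after outcomes are known, it could decide whether the trial succeeds.

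**Working it through.** **Inputs.** From *Sample size determination*: n = 38, p0 = 0.65, p1 = 0.85, two-sided exact test at 0.05, target enrolment 43. The allowance is 43 − 38 = 5, or 5/43 = 11.6%. Assumed, because the document gives neither: the number k of drop-outs in the FAS, and the probability c that a drop-out is scored as controlled.

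**Step 1: the plan's own figure.** For X ~ Bin(38, 0.65), the smallest r with P(X ≥ r) ≤ 0.025 is 31, and P(X ≥ 31) = 0.0205. With the lower rejection region (≤ 18) the attained two-sided level is 0.0398. Power is P(Bin(38, 0.85) ≥ 31) = 0.799. The stated 80% is reproduced for 38 patients.

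**Step 2: the FAS with 43 patients.** The upper cut is 35 (35/43 = 81.4%) and the lower region is ≤ 21. P(Bin(43, 0.65) ≥ 35) = 0.0149, and the two-sided total is 0.0363. Power is P(Bin(43, 0.85) ≥ 35) = 0.813. The exact 95% interval gives the same cut: its lower limit is 66.6% at 35/43 and 64.0% at 34/43. These figures require drop-outs to have the same control rate as everyone else.

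**Step 3: k drop-outs counted as controlled.** The remaining 43 − k patients must supply 35 − k controlled.

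| k | needed | upper-tail error | two-sided total | power |
|---|---|---|---|---|
| 0 | 35 of 43 | 0.0149 | 0.0363 | 0.813 |
| 2 | 33 of 41 | 0.0240 | 0.0349 | 0.848 |
| 5 | 30 of 38 | 0.0474 | 0.0506 | 0.894 |

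With k = 5 and a true rate of 65% in the other 38, the expected FAS rate is (5 + 0.65 × 38)/43 = 29.7/43 = 69.1%.

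**Step 4: k drop-outs counted as not controlled.** The remaining 43 − k must supply all 35.

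| k | needed | power | upper-tail error |
|---|---|---|---|
| 2 | 35 of 41 | 0.581 | 0.0033 |
| 5 | 35 of 38 | 0.158 | 0.0001 |

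If drop-out is random at 5/43 instead of exactly five, the FAS rate is 0.85 × 38/43 = 0.751, and P(Bin(43, 0.751) ≥ 35) = 0.223.

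**Step 5: between the extremes.** Five drop-outs, each controlled with probability c, are added to Bin(38, 0.85). Power is 56.3% at c = 0.50, 67.9% at c = 0.65, 78.2% at c = 0.80 and 81.3% at c = 0.85. Power stays within two points of 80% from about c = 0.80 up to at least 0.85.

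**The case against.** **Keeping 43 patients does no harm in itself.** This stands. If drop-outs do as well as the others, power is 81.3% and the attained two-sided level 0.036. A reader might infer that the planned analysis has neither its stated power nor its stated error rate. The documents do not support that. Scoring drop-outs as failures lowers power but makes a false claim of benefit less likely; scoring them as controlled raises both power and upper-tail error. The two harms do not occur together.

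**The 16% depends on a rule the protocol does not state.** This stands too. It would be wrong to say that the plan as written has 16% power. The last-evaluation rule tends towards scoring a drop-out as controlled.

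**The error inflation is small.** With five counted as controlled, the two-sided total is 0.0506, barely above the stated 0.05. The 0.025 limit for the upper tail is an equal split of that level, not a figure in the protocol. Even against 0.025, two such patients give 0.024. What remains is that the excess falls in the tail that supports a claim of benefit.

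**Few patients may be affected.** Patients who leave after starting treatment have clinical assessments within seven days of each fraction (*Patient follow-up*), so the baseline-only problem mainly concerns the never-treated, whose number is unknown.

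**The EAS is also analysed, and details can go in an analysis plan.** The EAS is supportive and its size is unknown, so it does not carry the 80% either. The protocol itself fixes the power basis, the efficacy set and the scoring rule, and the three do not fit together; this is more than an omitted detail. The *General* section calls all analyses descriptive, but the exact interval leads to the same cut of 35.

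**Conclusion.** The point holds in a limited form. The 80% is correct for 38 patients but is not established for the FAS, which is the primary efficacy set. Separately, the last-evaluation rule as worded allows a never-treated patient to count as controlled from a baseline evaluation.

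If all five allowance patients were scored that way, upper-tail error would go from 1.5% to 4.7%. If they were scored as not controlled, power would fall from 81.3% to 16%. Over all scorings of five drop-outs, power runs from 16% to 89%. Both ends assume that all five share one outcome; two drop-outs give 2.4% upper-tail error or 58% power. The number of drop-outs and their outcomes are assumptions throughout.

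**What to change.** Keep the FAS as primary and make three changes of wording before outcomes are known.

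1. In *Primary endpoint*, state that a baseline evaluation cannot count as local control at one year.
2. In the same place, state how FAS patients with no post-baseline evaluation are scored, for example as not controlled, with the EAS as the supportive analysis.
3. In *Sample size determination*, give an expected drop-out rate and restate power for 43 patients under that rule, with success at 35 or more of 43 (lower exact 95% limit above 65%).

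Moving the primary analysis to patients who received at least one fraction would not settle the matter. The sample size section does not describe such a set, and it would still contain patients who drop out after starting treatment.

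These changes need no more patients. The cost is that the restated power may be lower than 80%. If 11.6% were scored as not controlled (FAS rate 75.1%), regaining 80% would take about 164 patients, so the realistic choice is to report the lower figure openly.

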#### Patient accrual and study duration

We used an institutional database of patients with HNC and departmental treatment records to retrospectively approximate the number of patients that would have been eligible for this trial. Taking into account errors in electronic medical record documentation and coding [41, 42], we estimate that approximately 120–170 eligible patients were seen in our department over the past five years, roughly equating to two to three eligible patients monthly. These numbers are in line with or even slightly lower than what we have seen clinically recently, particularly as the COVID pandemic has subsided and more patients are being seen in our department. Additionally, our department’s recently closed phase II study of definitive HyperArc© SBRT in patients with recurrent, previously radiated HNC enrolled and treated the first fifteen patients in one year [15]. The patient population in this recently closed phase II trial is much narrower than that in the proposed study, so we anticipate similar if not faster enrollment with this proposed study compared with the recently closed phase II trial. As such, we anticipate enrollment of two to four patients monthly and that it will take approximately 15 months to complete the safety lead-in portion and 4 years to complete the study. Study-related data will be stored after completion of the clinical portion of the study to be used in the exploratory portion of the study, as needed.

#### Populations for analyses

##### Full Analysis Set (FAS)

All efficacy analyses will be performed on the Full Analysis Set (FAS) following the Intent-To-Treat (ITT) principle. Patients who were enrolled but did not receive study treatment are included in the FAS population.

##### Evaluable Analysis Set (EAS)

A subset of the full analysis set (FAS), the evaluable analysis set is defined as those treated patients who are evaluable (i.e. compliant with treatment and without any major protocol deviations that may impact primary efficacy analysis). The EAS will be used for supportive analyses of the efficacy endpoints.

##### Safety Analysis Set (SAS)

All patients who received at least 1 fraction of radiation and for whom any valid post-baseline safety data are available will be included in the safety analysis set. When assessing safety and tolerability, summaries will be produced based on the safety analysis set. Patients are analyzed according to the actual treatment received.

#### Study endpoints

##### Primary endpoint

The primary endpoint is local control rate of the treated tumor target at 1 year, as measured from the date of enrollment. Local control will be evaluated by radiographic and/or clinical assessment as applicable. Participants who experience death or are lost to follow-up prior to 1 year will be assessed by their last radiographic/clinical evaluation.

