#### PULSAR treatment

Daily cone-beam CT will be obtained prior to radiation delivery to verify anatomic location and stability. Treatment will consist of 6, 10, or 15 MV photons directed at the PTV using HyperArc©’s automated non-coplanar VMAT technique. Patients will receive a total of 55 Gray in 5 fractions (biological effective dose with alpha/beta of 10: 115.5 Gray) to the PTV. Patients will receive each 11 Gray fraction of radiation every 14 +/−10 days. Treatment will be terminated early in cases of intolerable treatment-related toxicity, altered clinical context, or the patient declines further treatment.

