#### Patient follow-up

Symptomatic response will be assessed through subjective patient report and completion of the UW-QoL and FACT-H&N questionnaires (Supplemental Material). Treatment-related toxicity during and after completion of PULSAR will be measured according to the CTCAE v5.0. Local tumor response will be assessed clinically and/or radiographically (e.g., by CT, PET, MRI), as applicable. Patient follow-up will be measured starting from the time of trial enrollment. Patient clinical assessments during PULSAR will occur within 7 days of each radiation treatment and consist of brief history, physical exam, and assessment of treatment-related toxicity. After receipt of the last PULSAR fraction, patients will be assessed clinically at 3 months +/- 28 days, 6 months +/- 28 days, 12 months +/- 28 days, 18 months +/- 28 days, and 24 months +/- 28 days post-treatment. These follow-up visits will consist of a history and physical exam, completion of the UW-QoL and FACT-H&N questionnaires, and measurement of toxicity. Surveillance imaging will be obtained per standard of care. Patients who experience disease progression will receive standard of care treatment(s) at the discretion of the treating physician. Patient enrollment, treatment, and follow-up is shown in Fig. 2.

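### The primary endpoint is read at 1 year from enrollment, but visits run from the last fraction, so on the nominal schedule no visit window contains day 365

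*Protocol article*

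**What the plan says.** The Primary endpoint section of the protocol article sets the landmark and its origin: "The primary endpoint is local control rate of the treated tumor target at 1 year, as measured from the date of enrollment". It adds "Local control will be evaluated by radiographic and/or clinical assessment as applicable", and for incomplete follow-up "Participants who experience death or are lost to follow-up prior to 1 year will be assessed by their last radiographic/clinical evaluation".

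The Patient follow-up section opens its timing with the same origin, "Patient follow-up will be measured starting from the time of trial enrollment", but then schedules the visits on another clock: "After receipt of the last PULSAR fraction, patients will be assessed clinically at 3 months +/- 28 days, 6 months +/- 28 days", followed by "12 months +/- 28 days, 18 months +/- 28 days, and 24 months +/- 28 days post-treatment". In the same section, surveillance imaging is left to standard of care with no protocol date.

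The PULSAR treatment section separates the two clocks: "Patients will receive each 11 Gray fraction of radiation every 14" days, with a tolerance of 10 days either way, for five fractions. The Radiation simulation section places simulation and planning after enrollment, without stating how long they take.

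**The concern.** Under Sample size determination the study is powered on a one-sample exact binomial test of 85% against 65% local control at 1 year, and the Efficacy analyses section reports a percentage with an exact interval. Each patient therefore needs a yes or no at day 365. On the nominal schedule a patient has a protocol visit at about month 8 and the next at about month 14, with nothing fixed between them.

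A failure that occurs between those visits and is first seen at the later one may have happened before or after day 365. If it is dated at detection, the patient counts as controlled at 1 year and the rate is too high. If the 14-month status is used as the 1-year status, failures that truly came after day 365 are counted and the rate is too low. The carry-back rule in the endpoint section covers only death and loss to follow-up, so it does not settle this case.

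**Working it through.** **The plan's own figure.** At n = 38 the two-sided exact binomial test of 65% at the 0.05 level rejects for 31 or more, or 18 or fewer, controlled. Its size is 0.040 and its power at 85% is 0.799, which reproduces the stated 80%. At the enrolled 43 the bounds are 35 or more, or 21 or fewer; power at 85% is 0.813, and the chance of 35 or more at 65% is 0.015.

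**Visit days from enrollment.** Visit day = L + sum of the four intervals between fractions + visit month x 30.44, with +/- 28 days. L is the time from enrollment to the first fraction. The protocol does not give L, so 0, 14 and 28 days are assumed.

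| Course | L | 6-month visit | 12-month visit |
|---|---|---|---|
| 4 x 14 = 56 days | 0 | 239 (211-267) | 421 (393-449) |
| 4 x 14 = 56 days | 14 | 253 (225-281) | 435 (407-463) |
| 4 x 14 = 56 days | 28 | 267 (239-295) | 449 (421-477) |
| one 35-day re-planning interval, 77 days | 0 | 260 (232-288) | 442 (414-470) |
| 4 x 24 = 96 days | 0 | 279 (251-307) | 461 (433-489) |

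No window in the table contains day 365.

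**When a window does reach day 365.**
- The 12-month window needs L + course of at most about 28 days. Four 4-day intervals (16 days) with L = 0 give 353-409; with L = 14 the window is already 367-423.
- The 6-month window needs L + course of at least about 154 days (365 - 183 - 28). Four 35-day intervals (140 days) with L = 14 or more achieve this.
- Stopping after one or two fractions shortens the course and can also bring the 12-month window to day 365.

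**Size if all patients are read at the 6-month visit.** Assume a constant failure hazard and true control of 65% at day 365, with the visit on days 239-260 (L = 0 to 21).
- 0.65^(239/365) = 0.754, and P(at least 35 of 43) = 0.24.
- 0.65^(260/365) = 0.736, and P(at least 35 of 43) = 0.16.

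The nominal value is 0.015.

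**Size if routine care finds a fraction f of the failures between that visit and day 365.** Apparent control = q - f(q - 0.65), where q is 0.754 or 0.736.
- f = 0.5: apparent control 0.702 or 0.693; chance 7.1% or 5.5%.
- f = 0.75: apparent control 0.676 or 0.671; chance 3.4% or 3.0%.

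The value of f is unknown.

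**Size if 14-month status replaces 1-year status.** Assume true control of 85% at day 365, with the visit on days 421-442.
- 0.85^(421/365) = 0.829, and P(at least 35 of 43) = 0.69.
- 0.85^(442/365) = 0.821, and P(at least 35 of 43) = 0.64.

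The value with correct reading is 0.81.

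**The case against.** **Assessment is not confined to visits.** Clinical and radiographic findings from routine care count, and scans may happen to fall near 1 year. This stands, and it is why the 16-24% is a bound. A reader might take it as the trial's actual false-positive rate. The documents do not support that, because it requires every patient to be read at one visit with no interval failure found.

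**The problem is not universal.** A reader might infer that no patient can have a planned visit near 1 year. The permitted 4-day intervals, very long courses and early stopping show otherwise. The statement holds for the nominal schedule and most permitted ones.

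**The downward error is conditional.** A patient still controlled at month 14 was controlled at 1 year, and a failure first documented after day 365 would ordinarily be dated after it. The power loss arises only if 14-month status is substituted. The two directions are therefore not equally likely.

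**Other analyses and documents.** Kaplan-Meier and cumulative incidence estimates are also planned. They use event dates, but a failure found at month 14 carries a date after day 365 and is missing from the 1-year estimate too. The analyses are called descriptive, and the 65% comparison appears only in the sample-size text; that limits the formal consequence, but the reported rate is still affected. The article condenses a fuller protocol, and the calendar figure is not shown, though its printed footnotes give no visit timed from enrollment. A windowing rule may well sit in an analysis plan, but it could not create an assessment that the visit schedule does not collect.

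**Each clock has a reason.** Enrollment suits an intention-to-treat analysis, and end of treatment suits toxicity follow-up. This is true, and the fix keeps both uses.

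**Conclusion.** The concern holds for the nominal schedule and most permitted ones. The endpoint and the visit calendar use different origins, day 365 falls in the gap between the 6- and 12-month windows, and no other assessment is fixed there. The more likely error is overstatement of 1-year control.

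Under a constant hazard, the chance of reaching 35/43 at a true 65% is at most 16-24% instead of 1.5%, and about 3-7% if routine care detects half to three quarters of the interval failures. If 14-month status is substituted, power at a true 85% is 64-69% instead of 81%. All of these depend on the assumed hazard shape and on planning time, which the protocol does not state.

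A reader might conclude that the sample size is wrong. It is not: 38 patients and 80% power reproduce, and neither changes. The timing should be settled before many patients pass the 1-year mark, because an assessment that was not made cannot be recovered.

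**What to change.** Keep enrollment as the origin of the primary endpoint. Time the existing 12-month efficacy assessment at 12 months +/- 28 days from enrollment (days 337-393), in place of 12 months after the last fraction. State that the primary endpoint is read from that window, using whatever clinical and standard-of-care imaging assessment is available in it. Leave the other visits timed from the last fraction for toxicity.

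Do not solve the mismatch by moving the endpoint's origin to the last fraction. The full analysis set includes enrolled patients who were never treated, and they have no last fraction.

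The cost is one change to the calendar and one to the endpoint definition, with no added visit and no new imaging requirement. The downside is that the retimed visit falls about 10 months after treatment (365 - 56 = 309 days with no planning time), so late-toxicity and quality-of-life reports at that visit no longer sit at 12 months after treatment.

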##### Efficacy analyses

Primary endpoint: Primary endpoint analyses will be performed on patients included in analysis sets FAS and EAS across the whole cohort, as well as separate analyses stratifying patients by Human Papillomavirus/p16 status and receipt of cancer-directed systemic therapy, both in general and by agent type (chemotherapy, targeted, immunotherapy). For the primary endpoint, we will calculate the percentage and construct 95% exact confidence interval for local control rate. Additionally, Kaplan–Meier method and cumulative incidence functions considering distant progression or death as a competing risk will be used to provide estimates of the local control at 1-year, median local control, and cumulative incidence of local control at 1-year, with corresponding 95% confidence intervals.Secondary Endpoints: Secondary endpoint analyses will be performed on patients included in analysis sets FAS and EAS across the whole cohort, as well as separate analyses stratifying patients by Human Papillomavirus/p16 status. For the secondary endpoints of PFS and OS, Kaplan–Meier method and cumulative incidence curves treating death as a competing risk will be used to provide estimates of the PFS/OS at 1-year, median PFS/OS, and cumulative incidence of PFS/OS at 1-year. Corresponding 95% confidence intervals will also be presented.

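### The primary percentage counts patients who die or are lost early without local failure as controlled at 1 year, so it overstates 1-year local control and rises with mortality

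*Protocol article*

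**What the plan says.** All places are in the protocol article.

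- **Primary endpoint:** "The primary endpoint is local control rate of the treated tumor target at 1 year, as measured from the date of enrollment". For patients without a full year of follow-up: "Participants who experience death or are lost to follow-up prior to 1 year will be assessed by their last radiographic/clinical evaluation".
- **Efficacy analyses:** "we will calculate the percentage and construct 95% exact confidence interval for local control rate". Kaplan-Meier and competing-risk estimates of 1-year local control follow in the same paragraph, but as additions to the percentage.
- **Sample size determination:** "A sample size of 38 patients will achieve 80% power to detect a 20% difference in the 1 year local control rate", comparing 85% with a historic 65%, "using a two-sided one-sample exact binomial test, at 0.05 significance level". The enrolment target is 43.
- **Full Analysis Set (FAS):** efficacy is analysed by intention to treat, and "Patients who were enrolled but did not receive study treatment are included in the FAS population". The Evaluable Analysis Set (EAS) is supportive.
- **Study population:** patients may have metastatic disease, comorbidities or poor performance status. Patients with localized disease who decline definitive treatment may also enter. No survival figure is given.

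**The concern.** Read together, these sections fix how an early death or loss is scored. If the last evaluation showed local failure, the patient is a failure. If it did not, the patient is a success at 1 year and stays in the denominator, although the tumour was never observed at 1 year and any later failure cannot be seen. The percentage therefore estimates the proportion with no local failure before death, loss or 1 year. That is always at least as high as true 1-year local control, and it grows with early mortality.

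At stake is the meaning of a positive primary result. If the 65% benchmark is a true or actuarial 1-year rate, a regimen that controls tumours no better than 65% gains an advantage simply because some patients die before they can fail locally.

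**Working it through.** **Reproducing the plan's figure.** Inputs from Sample size determination: null 65%, alternative 85%, two-sided exact binomial test at 0.05, so at most 0.025 in the upper tail.

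- n = 38: reject at 31 or more controlled. P(X ≥ 31 | 38, 0.65) = 0.0205 and P(X ≥ 31 | 38, 0.85) = 0.799. The stated 80% power reproduces.
- n = 43: reject at 35 or more. The exact 95% lower limit is 64.0% for 34/43 and 66.6% for 35/43. P(X ≥ 35 | 43, 0.65) = 0.0149 and power at 85% is 0.813.

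**Effect of the last-status rule.** Assumptions, because the article gives no mortality: constant, independent hazards of local failure (λ) and death (μ), failures seen when they occur, and true 1-year local control exactly at the 65% null.

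- λ = −ln 0.65 = 0.4308; μ = −ln S, where S is 1-year survival.
- Expected last-status percentage = 1 − [λ/(λ+μ)] × [1 − exp(−(λ+μ))].
- Example, S = 0.70: μ = 0.3567; λ+μ = 0.7875; exp(−0.7875) = 0.65 × 0.70 = 0.455; λ/(λ+μ) = 0.547. Result: 1 − 0.547 × 0.545 = 0.702.
- The chance of a result above 65% is then P(X ≥ 35 | 43, that percentage).

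| Assumed 1-year survival | Expected percentage | Chance of ≥ 35/43 |
|---|---|---|
| 100% | 65.0% | 1.5% |
| 90% | 66.7% | 2.5% |
| 80% | 68.4% | 4.3% |
| 70% | 70.2% | 7.1% |
| 50% | 74.1% | 18.2% |
| 40% | 76.3% | 28.1% |

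The nominal level per side is 2.5%; the 1.5% in the first row is what the exact test attains at n = 43.

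**A check without hazards.** Take 38 analysed patients, 8 of whom died or were lost early while last seen controlled. Rejection needs 31 − 8 = 23 of the other 30. If those 30 have 65% control, the expected percentage is (8 + 0.65 × 30)/38 = 72.4%, and P(X ≥ 23 | 30, 0.65) = 12.4% instead of 2.05%. With 4 such patients it is 5.3%; with 12, 26.0%.

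**Do the additional analyses remove the problem?** Under the same assumptions, the cumulative incidence of local failure with death competing is [λ/(λ+μ)] × [1 − exp(−(λ+μ))]. One minus this is exactly the expected last-status percentage, so the competing-risk estimate shares its dependence on mortality. Kaplan-Meier with censoring at death targets the 65% itself. In simulation (n = 43, same hazards, log-log 95% CI with lower limit above 65%), it rejects in 1.4 to 2.0% of trials under the null.

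**The case against.** **The benchmark may be of the same kind.** The 65% is drawn from a prospective 60% rate, retrospective series of 69 to 87%, and regimens described only as doing less well. The article does not say whether these are actuarial, competing-risk or crude last-status rates. A reader might infer that the comparison with 65% is certainly biased towards PULSAR; the document does not establish that. If the 65% is a crude rate from patients with similar mortality, the bias against it is smaller. The overstatement of true 1-year control stands either way.

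**Mortality may be modest.** A reader might infer that early death will be common. The article gives no rate, and the population includes patients with localized disease who simply decline treatment. At 90% survival the error chance is about the nominal 2.5%. This stands, and it is why the whole range is shown.

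**The drop-out allowance.** The article says: "Considering that some patients may become ineligible/drop out after enrollment, the target sample size is determined to be at least 43 patients". The FAS nevertheless keeps untreated patients, so a reader might work out large error rates or power losses by scoring five such patients all as controlled, or all as failures. The two scorings contradict each other, and the text fixes neither. With 43 analysed the power is 81.3%, so keeping everyone in the FAS does no harm in itself.

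**Already covered, and descriptive.** Kaplan-Meier is planned, the General section calls all analyses descriptive, and no pass/fail rule is stated. But the percentage is the quantity that the sample size tests, and Kaplan-Meier is only additional.

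**Kaplan-Meier has its own weakness.** Censoring at death assumes that death is independent of local failure. The Background says that locoregional progression often causes death in this disease, so the assumption is doubtful. If patients near death are also those about to fail locally, Kaplan-Meier still overstates control. This objection stands and must be declared with the result.

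**Conclusion.** The point holds. The stated rule and the crude percentage together overstate true 1-year local control, by an amount that rises with early mortality. The direction is certain because failures after early death or loss are never observed. Deaths after documented local failure are correctly counted as failures and do not contribute.

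The size rests on assumed survival and on constant independent hazards. With true control of 65%, the percentage is inflated by 1.7 points at 90% survival, 5.2 at 70% and 11.3 at 40%. The chance of an exact lower limit above 65% goes from 1.5% to between 2.5% and 28.1%. These error rates apply if the 65% is a true or actuarial 1-year rate.

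**What to change.** 1. Make the already planned Kaplan-Meier estimate of 1-year local control, with a log-log 95% CI, the primary comparison with 65%. Censor death or loss without local failure at the last evaluation.
2. Keep the FAS as the primary set and the EAS as support. Untreated patients without local failure are then censored at their last evaluation rather than scored as successes.
3. Report two labelled sensitivity analyses: the last-status percentage, and the cumulative incidence of local failure with death competing. Give the number of deaths before 1 year without local failure.
4. State that censoring at death assumes independence from local failure.
5. State how the 65% was estimated, so that estimate and benchmark can be seen to be on the same scale.

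Scoring every early death as a failure is not an easy alternative. At 90% survival, 85% control becomes 0.85 × 0.90 = 76.5% and power with 38 patients is about 30%, so benchmark and sample size would both have to be reset.

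**Cost.** No new data are needed, but this is more than rewording, because power must be restated. With 43 patients and 85% control, simulation gives about 77, 70 and 58% at assumed 1-year survival of 90, 70 and 50%, instead of the stated 80% (repeat runs differ by a point or two). The trial must either accept that power or recompute its sample size.
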